### Process evaluation

A process evaluation will be conducted to evaluate whether the intervention was carried out in accordance with the trial protocol. Specifically, all PST consultations will be taped and 1/3 of them will be reviewed by the research team to ensure the fidelity of this intervention. The fidelity of the ‘referral to GP’ arm will be determined by noting the date the referral letter was sent to the GP. After the 6 month outcome measure a letter will be sent to each participant’s GP asking what treatments / action have taken place during the trial period. At the end of the trial all participants will take part in an interview to determine their level of satisfaction with the service received and any action taken by the GP. This final interview will include qualitative questions about what worked well and not so well.

### Assessment of costs

We will also conduct an assessment of the direct costs associated with the delivery of the PST intervention and identify its key cost consequences e.g. reductions in demands on other service. The cost of the intervention will be assessed by monitoring the activity of the Psychological Therapist and the costs associated with travel to and from participants’ homes.

The costs associated with the use of additional services will be established using a telephone based Client Service Receipt Inventory (CSRI) [21].

### Analyses

#### Statistical analyses

We will tabulate the number of patients by GDS-15 Score. We will estimate the prevalence of depressive symptoms (defined as a GDS-15 score of 6 or more) with 95% confidence intervals computed by the exact binomial method. We will use logistic regression to assess whether factors such as age, sex, pathology and site are associated with depressive symptoms. With a sample size of 1000, a two sided 95% confidence interval will extend 0.028 from the observed proportion for an expected proportion of 0.3.

This trial is the first of its kind and hence ‘exploratory’. For the trial, we will compare baseline characteristics of the allocated groups to ensure the adequacy of randomisation (including duration of visual loss). If outcome data are not available for all randomised patients, we will compare characteristics of those for whom it is available with those for whom it is not to assess whether the groups differ systematically. To retain the validity of the randomisation process the analyses will be undertaken on an intention-to-treat basis.

We will report average change in BDI scores in treatment groups using the mean or median as appropriate together with some indication of variability such as the standard deviation or interquartile range. These results will then be used to estimate the numbers of patients required for a definitive study.

Missing data has the potential to bias our findings. Hence we will attempt to minimise ‘loss to follow up’ by making it clear to potential recruits what is required at the outset, letting them know that completion of the study is important and reminding them of the value of their contribution when outcomes are assessed during the scripted telephone interviews. We will document the reasons for missing data and establish both the extent and patterns of missing data in each arm of the trial. We will also acknowledge the potential impact of missing data in our conclusions.

We will also compare the characteristics (age, sex, level of depression, level of vision impairment, ethnicity, functional ability and time since vision loss first identified) of those who did and did not consent to take part in the trial to determine if we can predict who is likely to benefit from depression screening.

We will also look for PST trainer effects (i.e. compare outcomes of PST delivery in London and Wales). The study design and scripted outcome measurements are designed to minimise the possibility of masking violation in this exploratory trial. We will however report any masking violations descriptively.

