**Methods /design:**

The study is an exploratory, multicentre, individually randomised waiting list controlled trial. Participants will be randomised to receive Problem Solving Therapy (PST), a ‘referral to the GP’ requesting treatment according to the NICE’s ‘stepped care’ recommendations or the waiting list arm of the trial. The primary outcome measure is change (from randomisation) in depressive symptoms as measured by the Beck’s Depression Inventory (BDI-II) at 6 months. Secondary outcomes include change in depressive symptoms at 3 months, change in visual function as measured with the near vision subscale of the VFQ-48 and 7 item NEI-VFQ at 3 and 6 months, change in generic health related quality of life (EQ5D), the costs associated with PST, estimates of incremental cost effectiveness, and recruitment rate estimation.

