The Depression in Visual Impairment Trial (DEPVIT) will establish depression screening in several UK based vision rehabilitation centres and obtain preliminary data about the treatment effects associated with the stepped care approach recommended by NICE and PST. More specifically, DEPVIT aims to estimate the prevalence of depressive symptoms using the Geriatric Depression Scale (GDS-15) in an observational study of consecutive attendees of low vision services in England and Wales, and compare 2 interventions, PST and ‘referral to the GP’, against a waiting list control for newly-diagnosed low vision patients with depressive symptoms in an exploratory randomised controlled trial. Subsidiary aims include determining what action GPs take in response to a referral for depressive symptoms in this patient group, determining the acceptability of these interventions to patients and establishing economic information about the cost to roll-out a psychological problem solving based intervention for people experiencing sight loss and how well standard economic tools work with people experiencing sight loss.

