### Outcome measures

The primary outcome will be the change in depressive symptoms, from randomisation to 6 months, as measured by the Becks Depression Inventory (BDI-II). The BDI-II is a reliable, valid and widely used outcome measure for depression [16,17].

Secondary outcome measures in this exploratory trial will include change (from randomisation to 3 and 6 months) in visual disability as measured using the 7 item NEI VFQ and the near vision subscale of the VFQ-48 and, change in ‘generic health related quality of life’ as measured using the EQ-5D [18,19]. Additional secondary outcomes measured at 6 months will include the proportion of people still screening positive for depression as measured with the GDS-15, participant’s use of services as determined using a Client Services Receipt Inventory (CSRI) and an economic measure of ‘capability and wellbeing’ the ICECAP-O [20]‐[22]. At the end of this exploratory trial participants will be asked about any treatments for depression they have received during the trial period (specifically, whether they received regular review and support by their GP, referral to a community mental health team, supportive psychotherapy, counselling, problem-solving therapy, cognitive-behavioural therapy or antidepressant therapy). They will also be asked about the acceptability of any interventions received. Participants in the waiting list control group who still screen positive for depression (GDS-15, 6+) will be referred to their GP. And, 3 months later asked about any treatment for depression received as a result of the referral.

All trial outcomes will be assessed by telephone interview by the Study Coordinator who will be masked to the treatment intervention. In order to minimise ‘loss to follow up’, interviews will be based on a standard script and will remind participants of their valuable contribution and the need to complete the study.

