### Sample size

During the course of the study 1000 consecutive attendees will be screened. At the outset we anticipate that about 1/3 will screen positive for depression and be eligible, and that of those, about 100 will consent to take part. This target of 100 patients recruited into the trial is realistic and achievable. Resource limitations require us to cap the number of participants to 150.

Since this study is exploratory we will predominantly use descriptive methods to report results. That is, this study is not powered to look at differences in outcomes (there is no data upon which to determine the sample size). However, to give the reader some indication about the power of this exploratory trial, if we assume that those entering the trial are moderately depressed (average BDI-II score of 30, SD 10.5) and, if the trial finishes with only 20 participants per treatment group, we would have 83% power to detect a difference in post treatment means of 10 (a change of 10 units corresponding to a moderately important clinical difference) with a 5% two-sided significance level.

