Potential recruits who would like additional time to consider enrolment, after the initial low vision assessment will be contacted by phone by their low vision practitioner one week later to find out “how they are getting on”. If they then want to take part in the study they will be booked back in to see the practitioner to complete the study consent form. Participants who screen positive for depression but who decline to take part in the trial will be asked if they would like to be referred to their GP anyway. The person’s decision will be noted in the records e.g. if they decline referral. These people will be asked if they are willing to provide their consent for the use of anonymous baseline data.

Within one week of the baseline telephone interview, participants will be randomised using computer generated permuted blocks of varying sizes (unknown to investigators) stratified for study centre (Wales and London) and for ‘medication evaluation’ only. To ensure that the Study Coordinator is masked to treatment allocation, the Chief Investigator will allocate participants to the different arms of the trial.

For those assigned to the ‘referral to GP’ arm of the trial, the letter to the GP will be posted on the day the person was randomised and the participant will be asked to make an appointment with their GP within 2 weeks. For those assigned to PST, treatment will commence within 2 weeks of randomisation. All participants will be given a follow up vision rehabilitation appointment 6 weeks after the initial rehabilitation appointment.

The Study Coordinator will contact participants 3 and 6 months after randomisation to obtain outcome measure data.

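### The stated analysis of the primary outcome summarises BDI-II change arm by arm; a between-arm difference with a confidence interval, adjusted for baseline, would serve the trial's stated comparison better at no cost

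*Protocol article*

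**What the plan says.** All references are to the protocol article; no statistical analysis plan is shown.

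- **Aim** (Background, last paragraph): the randomised part will "compare 2 interventions, PST and ‘referral to the GP’, against a waiting list control".
- **Primary outcome** (Outcome measures): change in BDI-II from randomisation to 6 months.
- **Analysis of that outcome** (Statistical analyses): "We will report average change in BDI scores in treatment groups using the mean or median as appropriate together with some indication of variability", the variability being an SD or an interquartile range. The next sentence says that these results will be used to size a definitive study.
- **Stance** (Sample size): "Since this study is exploratory we will predominantly use descriptive methods to report results".
- **Power illustration** (same section): 83% for a difference of 10 in post-treatment means, SD 10.5, 20 per arm, two-sided 5%.
- **Randomisation** (Trial procedures): "stratified for study centre (Wales and London) and for ‘medication evaluation’ only". A medication evaluation is requested when baseline BDI-II is 29 or more.

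**The concern.** The aim and the power illustration are between-arm, while the one analysis stated for the primary outcome is within-arm. Elsewhere the same section is specific. Prevalence gets an exact 95% interval and a logistic regression, and PST outcomes are to be compared between London and Wales. So a non-randomised comparison inside one arm is named, and the randomised comparison on BDI-II is not.

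Change within an arm is not a treatment effect here. Four influences act on every arm:

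- likely regression to the mean, because entry requires a GDS-15 score of at least 6;
- natural recovery;
- the rehabilitation follow-up at 6 weeks, given to all;
- the GP letter for everyone with baseline BDI-II of 29 or more, the waiting list included.

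Only the contrast with the waiting list removes them. What is at stake is how directly the trial delivers its treatment-effect estimate, and whether the definitive trial is sized on the right quantity.

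**Working it through.** **1. The article's own figure.** Inputs from Sample size: n = 20 per arm, difference 10, SD 10.5, two-sided 5%. The noncentrality is 10 / (10.5 × √(2/20)) = 3.01. A two-sample t-test on 38 degrees of freedom then has power 83.5%, which matches the stated 83%. (The normal approximation gives 85.4%.) The illustration is therefore a between-arm t-test on 6-month scores. That test does not appear in Statistical analyses, and it is on a different scale from the change score.

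**2. How many participants receive the shared GP letter.** With the article's mean of 30 and SD of 10.5, and assuming normality, P(BDI-II ≥ 29) = P(Z ≥ (29 − 30)/10.5) = P(Z ≥ −0.095), about 54%. The shared influence is not marginal.

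**3. What sizing the next trial needs.** The required n is proportional to SD²/δ², where δ is the between-arm difference. If the shared improvement is s, an active arm's own change estimates δ + s. Anyone who took that change as the effect would understate n by the factor (δ/(δ + s))². Means, SDs and numbers by arm allow a crude δ to be derived by subtraction. Medians with interquartile ranges do not give it directly.

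**4. Precision of two between-arm estimates.** The assumptions, neither of them in the article, are an SD of 10.5 at both times and a baseline to 6-month correlation r.

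- SD of change = 10.5 × √(2(1 − r))
- Residual SD after baseline adjustment = 10.5 × √(1 − r²)
- Half-width of the 95% interval = t(0.975; 38) × SD × √(2/20)
- Variance ratio, adjusted to change = (1 + r)/2

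| r | SD, change | SD, adjusted | Half-width, change | Half-width, adjusted | Power, change | Power, adjusted | Variance ratio |
|---|---|---|---|---|---|---|---|
| 0.3 | 12.42 | 10.02 | 7.95 | 6.41 | 69.9% | 86.8% | 0.65 |
| 0.5 | 10.50 | 9.09 | 6.72 | 5.82 | 83.5% | 92.3% | 0.75 |
| 0.7 | 8.13 | 7.50 | 5.21 | 4.80 | 96.6% | 98.4% | 0.85 |

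The degrees of freedom are held at 38 throughout to stay comparable with step 1; the one or more lost to covariates are ignored. Power is for a difference of 10.

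The quoted 83% carries over to a simple difference in change only if r is about 0.5 or more. Baseline adjustment is better at every r in the table, but the advantage shrinks as r rises.

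**The case against.** The strongest reply is that the design is declared. The trial is called exploratory, its reporting predominantly descriptive, and the article says "this study is not powered to look at differences in outcomes (there is no data upon which to determine the sample size". Summaries by arm with an SD feed the planning of a larger trial, and covariates, strata and models are commonly left to an analysis plan. Much of this stands. It justifies leaving out a hypothesis test. It does not explain leaving out the randomised estimate, since a difference with an interval is itself descriptive and prevalence already gets an interval.

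A reader might infer more than the article supports:

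- *That the trial cannot answer its own comparison.* The waiting list is a concurrent randomised control reported alongside the others. With means, SDs and numbers, a crude difference and interval can be derived, and the word predominantly leaves room for a contrast. Analyses of costs also plans an incremental comparison with GP referral and the waiting list, with GDS-15 as the effect measure.
- *That only completers are averaged.* The article does not say so. It states intention-to-treat, a comparison of those with and without outcomes, and reporting of missing data by arm.
- *That baseline and strata are excluded.* They are not mentioned in this analysis, which is not the same thing.
- *That every arm will certainly improve.* Selection is on the GDS-15, while BDI-II is a different instrument given later with no minimum score for entry. Regression to the mean is likely, but weaker than if BDI-II itself were the entry score.
- *That power is being lost now.* No change-score test is proposed. The table compares two ways of forming a contrast that the article has yet to name.

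**Conclusion.** The point holds as a moderate, no-cost improvement. It rests on a stated method rather than on missing detail: the summary named for the primary outcome is within-arm, while the aim, the power illustration and the intended use for sizing all call for a between-arm difference.

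The gain from adding baseline adjustment depends on the assumed correlation. The half-width falls by about 19% at r = 0.3 (7.95 to 6.41) and about 8% at r = 0.7 (5.21 to 4.80). The calculation assumes equal SDs at both times and 20 per arm. No further gain is claimed for the strata, because the medication-evaluation stratum is a cut of baseline BDI-II and largely overlaps with it. A must-fix rating, or insistence on one particular repeated-measures model, would go beyond what the article supports in an exploratory, unpowered trial.

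**What to change.** In Statistical analyses, after the sentence on average change, add wording such as: *We will estimate the difference in mean 6-month BDI-II between PST and waiting list, and between GP referral and waiting list, each with a 95% confidence interval, from a linear model adjusted for baseline BDI-II and the stratification factors. These estimates are exploratory.*

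The primary outcome need not be redefined. With baseline in the model, the estimated arm difference is the same whether the dependent variable is the 6-month score or the change.

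Then:

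- report means and SDs by arm, with medians and interquartile ranges only as a supplement;
- keep change within each arm as description;
- say that the definitive trial will be sized from the between-arm estimate and its variability;
- align the illustration in Sample size with this analysis, stating the correlation assumed.

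The cost is wording only. Baseline and 6-month BDI-II, centre and medication-evaluation status are already collected, and no extra participants or contacts are needed.

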### The interventions

This trial involves 2 active interventions PST and ‘referral to the GP’ and a ‘waiting list control’.

The PST intervention evaluated in this study is a behavioural therapy that has been specifically designed for people with a visual impairment [8]. This intervention involves a trained psychological therapist working with the patient in their own home or at one of the research centres. Over a 6–8 week period, patients are taught a 7-step method for approaching and solving their problems. The steps are: (1) defining the problem; (2) establishing realistic goals; (3) brainstorming solutions; (4) implementing decision making guidelines (Pros versus Cons); (5) choosing a preferred solution; (6) implementing the solution; and (7) evaluating the outcome. The PST intervention will also include additional self-help materials for patients e.g. materials concerning an explanation of depression, a discussion on the importance of treating depression, and a description of the various treatment options as well as vision related sign posting materials. This type of behavioural therapy is an individualised guided self help approach consistent with NICE guidelines [15]. Optometrists providing the low vision assessment will share the patient’s ‘treatment plan’ with the therapist (via a brief report) so that the therapist can help the patient implement the optometrist’s recommendations via the PST framework if this is what the patient wishes. To ensure the fidelity of this intervention the PST therapists will be trained by [name] the Clinical Psychologist who originally designed the PST intervention used in 2007 by Rovner, Casten et al, [8]. With the participants consent, each PST intervention will be taped and one third of randomly selected tape recordings will be reviewed to ensure the fidelity of the intervention.

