### Recruitment

Participants will be identified and recruited from 7 community based low vision rehabilitation centres in South Wales and from one large secondary care based low vision rehabilitation centre at Guys and St Thomas’ NHS Trust, London [23]. Based on known activity in these recruitment centres we anticipate that the 7 sites in Wales will screen approximately 500 people in total and that a similar number will be screened in London.

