### Challenges

Encouraging those with depression to engage with the research project may be challenging given that their motivation is likely to be low. By getting their optometrist, who has provided the vision rehabilitation intervention, to describe the study and ask for consent we hope to maximise recruitment.

The relationship between depression and visual impairment is complex [13]. Hence, good outcomes are most likely to be observed following good vision rehabilitation and depression interventions i.e. both are required. Whilst the research team have good control of the depression interventions and will check their fidelity we are not checking the rigor of the vision rehabilitation interventions. The optometrists providing the vision rehabilitation in Wales have been trained and accredited, by Cardiff University, to provide a very specific type of community based intervention delivered as part of the “Welsh Low Vision Service” [23,30]. The optometrists at the London site are experienced vision rehabilitation practitioners but they have not been trained and accredited in the same way. To minimise any differences in the vision rehabilitation intervention the clinical leads of the Welsh and London services have met to agree to a standardised approach to low vision rehabilitation. This standardised approach is documented in the master files at all sites.

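### The look for PST trainer effects is a comparison of PST outcomes between London and Wales, so a difference cannot be attributed to the trainer or therapist

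*Protocol article*

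**What the plan says.** At the end of Statistical analyses the protocol article states: "We will also look for PST trainer effects (i.e. compare outcomes of PST delivery in London and Wales"). The parenthesis makes the comparison of the two centres the definition of a trainer effect. That sentence mentions neither the control arms nor any adjustment.

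Other sections describe how the centres differ:

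- **Setting.** Recruitment names "7 community based low vision rehabilitation centres in South Wales and from one large secondary care based low vision rehabilitation centre", the latter in London.
- **Vision rehabilitation.** Challenges explains that the Welsh optometrists are trained and accredited for a specific community service. Of the London optometrists it says "they have not been trained and accredited in the same way". The same section says "we are not checking the rigor of the vision rehabilitation interventions", and that good outcomes are most likely when both the rehabilitation and the depression treatment are good.
- **Mitigation.** Challenges also reports that "the clinical leads of the Welsh and London services have met to agree to a standardised approach to low vision rehabilitation", and that the agreed approach is documented at all sites.
- **PST training and fidelity.** Under The interventions, one clinical psychologist, the designer of the intervention, trains the PST therapists. A third of session tapes are reviewed.
- **Randomisation.** The section on trial procedures stratifies by study centre (Wales and London) and by medication evaluation.

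**The concern.** Arms are randomised within centre, but patients are not randomised between centres. Comparing PST patients in London with PST patients in Wales is therefore an observational comparison, although the sentence labels its result a trainer effect. The protocol itself identifies a between-centre factor, the vision rehabilitation, that it expects to influence outcome. A difference arising from rehabilitation or setting would also appear in the waiting-list arm, but the stated comparison does not look there.

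Patient mix may differ too. That is an inference: the documents give no case-mix figures by centre, although site is listed among the factors to be examined for association with depressive symptoms.

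The Discussion says the trial's data will inform a phase III trial. A centre difference labelled as a trainer effect could suggest that PST delivery varies when it does not. A true difference in delivery could equally be hidden by an opposite centre difference.

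**Working it through.** **Inputs.** From Sample size: BDI-II SD 10.5, 20 participants per arm at the end of the trial, two-sided 5% level, recruitment target 100, cap 150. Assumptions: three equal arms, an equal London/Wales split (Recruitment expects about 500 people screened in each, but gives no split for those randomised), and SD 10.5 applied to the outcome compared. If that outcome is change from randomisation, its SD is 10.5 × √(2(1 − r)), where r is the correlation between baseline and 6 months. This equals 10.5 only at r = 0.5.

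**The plan's own figure.** A two-sample t-test with difference 10, SD 10.5 and 20 per arm at two-sided 5% has 83.5% power, which reproduces the stated 83%. No precision or power is stated for the trainer comparison.

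**Precision of the two contrasts.** Let n be the number of patients per arm per centre.

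- PST only, London minus Wales: SE = 10.5 × √(2/n).
- (PST minus waiting list) in London minus the same in Wales: SE = 10.5 × √(4/n).

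Half-width of the 95% CI = 1.96 × SE:

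| n per cell | Corresponds to | PST only | PST minus waiting list |
|---|---|---|---|
| 10 | 20 per arm | 9.2 | 13.0 |
| about 16.7 | 100 in total | 7.1 | 10.1 |
| 25 | 150 in total | 5.8 | 8.2 |

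For n = 10 with t quantiles:

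- PST only, 18 df: 2.10 × 4.70 = 9.9.
- Controlled contrast, pooling the variance over all six arm-by-centre cells, 54 df: 2.005 × 6.64 = 13.3.

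The controlled interval is thus wider by 13.3/9.9 − 1, about 35%, on t quantiles, and by √2 − 1, about 41%, on the normal quantile.

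**What a centre difference does.** Suppose no therapist effect and a centre difference of b points from other causes, the same in every arm. The PST-only comparison estimates b. The controlled contrast estimates b − b = 0. The chance that the PST-only comparison is significant at two-sided 5% is Φ(b/SE − 1.96) + Φ(−b/SE − 1.96):

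| b (assumed) | n = 10 | n about 16.7 | n = 25 |
|---|---|---|---|
| 2 | 7% | 9% | 10% |
| 5 | 19% | 28% | 39% |
| 10 | 57% | 79% | 92% |

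The documents give no value for b, so the range is illustrative. The chance rises with sample size because the cause is bias, not noise.

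**Limit of the cancellation.** If rehabilitation quality changes how well PST works, so that the centre effect is b₁ under PST and b₀ on the waiting list, the controlled contrast still contains b₁ − b₀. The protocol makes this plausible: the therapist may help the patient carry out the optometrist's recommendations.

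**The case against.** The case for leaving the text alone has substance.

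- **It is one sentence in a condensed article.** It fixes no estimator and does not exclude adjustment or use of the controls, and model detail may sit elsewhere. That stands as to detail. It does not rescue the definition, which equates a centre comparison with a trainer effect.
- **The centres are less different than they might be.** The agreed rehabilitation approach and the tape review both help, and the tapes check delivery without relying on outcomes. These reduce the problem. They do not remove it, because rehabilitation is unchecked and setting still differs.
- **The outcome is change from randomisation.** This deals largely with differences in baseline level, but not with differences in prognosis or in rehabilitation received.
- **The controlled contrast is noisy and only partly clean.** Both points are correct. With 20 per arm its half-width exceeds the 10-point difference in Sample size.
- **The trial is exploratory and mainly descriptive.** This limits the importance of the point and does not alter it.

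Two stronger readings are tempting and not supported. A reader might infer that, since The interventions says "To ensure the fidelity of this intervention the PST therapists will be trained by" a single psychologist, London versus Wales cannot be a trainer contrast at all. But trainer most plausibly means the therapist who teaches patients the seven steps, and the parenthesis speaks of PST delivery, so the shared training is no contradiction. A reader might also infer that patient mix is known to differ, or that the result will decide therapist training. The documents give no case-mix data by centre and state no such use.

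**Conclusion.** The point holds in a limited form. A difference in PST-arm outcomes between London and Wales cannot be attributed to the trainer or therapist, because centre is not randomised and the protocol documents differences in setting and in optometrist training, with unchecked rehabilitation that it expects to matter. The documented differences suffice; patient mix remains a possibility only.

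The size of any distortion is unknown, since it equals whatever centre difference exists. For assumed differences of 2, 5 and 10 points, the chance of a misleading significant result is 7–10%, 19–39% and 57–92%, given SD 10.5, equal arms and an equal centre split. With 20 per arm, neither contrast is precise enough for a null result to be read as no difference.

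Importance is modest. This is a subsidiary look in an exploratory trial, and the primary randomised comparison is untouched.

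**What to change.** Replace the sentence under Statistical analyses with wording such as: *We will report change in BDI-II at 6 months by arm and centre, and estimate the difference between London and Wales in the PST-minus-waiting-list contrast, with its 95% confidence interval. This will be described as an exploratory centre difference in the effect of PST. It will not be attributed to trainer or therapist, and a non-significant result will not be read as no difference.*

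Add that the contrast removes centre differences common to both arms, but not centre factors that modify the effect of PST, such as rehabilitation quality.

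The cost is a few lines of text. No new data and no change to trial conduct are needed, since the stratified randomisation already supplies the controls. The article states no regression model for BDI-II change, and none is required: the contrast can be formed from the four cell means and SDs. The price is an interval about 35% to 41% wider with 20 per arm (about 13 points against 9 to 10).
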